## Abstract

Intermittent theta burst stimulation (iTBS), a variant of repetitive transcranial magnetic stimulation (rTMS), is an established treatment for adults with major depressive disorder (MDD). Due to its favorable safety profile, iTBS is also a promising early intervention in the transition phase from adolescence to early adulthood, but this has not been systematically investigated to date. Thus, the EARLY-BURST trial investigates the efficacy and safety of iTBS over the left dorsolateral prefrontal cortex (lDLPFC) in treatment-seeking young patients (age 16–26 years) with depressive disorders (i.e. major depressive disorder, persistent depressive disorder, bipolar depression), allowing for relevant co-morbidities. Participants have not received antidepressant or antipsychotic medication during the last 12 months except for short-term (< 2 weeks) on-demand medication. The trial will employ a novel sequential Bayesian, randomized, double-blind, parallel-group, sham-controlled design. Up to 90 patients at two clinical sites (Munich, Augsburg) will be randomized 1:1 to the treatment groups, with sequential analyses starting after 26 patients in each group completed the treatment. The primary outcome will be the difference in depression severity at week 6 (post-treatment visit) between active iTBS and sham iTBS, assessed with the Montgomery-Åsberg Depression Rating Scale (MADRS). The trial is planned to be expanded towards a three-arm leapfrog design, contingent on securing additional funding. Thus, in addition to potentially providing evidence of iTBS’s efficacy in adolescents and young adults with depressive disorders, the EARLY-BURST trial aims at setting the stage for subsequent platform trials in this dynamic research field, where novel adaptive study designs are required to meet the need for rapidly testing promising new vs established rTMS protocols.

*Trial registration:* DRKS00033313.

## Background

Depressive disorders emerge with a first peak age of onset of 20.5 years [1] and are a major contributor to the global burden of disease among adolescents and young adults [2]. Current neurobiological treatments for this demographic are often adapted from adult treatments with minimal adjustments and have limited supporting evidence [3]. Consequently, prioritizing the development of early interventions for depression has been recognized as crucial by patients, informal carers, and clinicians (https://www.jla.nihr.ac.uk/priority-setting-partnerships/depression/).

Repetitive transcranial magnetic stimulation (rTMS) of the dorsolateral prefrontal cortex (DLPFC) is an effective, well-tolerated treatment option for adults with major depressive disorder (MDD) who have not sufficiently benefitted from antidepressant pharmacotherapy, as demonstrated by multicenter trials [4–6]. A recent meta-analysis supports the notion that rTMS of the DLPFC might even qualify as an antidepressant therapy across diagnostic categories [7]. In contrast, the application of rTMS for treating depressive disorders in adolescents and young adults has yielded mixed results. A recent meta-analysis encompassing both open-label and randomized controlled trials (RCT) revealed significant but heterogeneous effects of rTMS on depressive symptoms and response rates among young patients [8]. The largest RCT in adolescents to date even failed to show superior effects of a conventional 10 Hz rTMS protocol compared to sham in patients with non-response to 1–4 adequate pharmacological trials [9]. Conversely, a smaller RCT employing neuronavigation-guided, high-frequency rTMS reported significant short-term amelioration of suicidal ideation in treatment-naive patients with MDD [10]. Furthermore, an open-label trial suggested that intermittent theta burst stimulation (iTBS), a newer and shorter rTMS protocol established in adults [5, 11], might be a feasible and effective treatment option for adolescents [12], although a subsequent RCT comparing once and twice-daily TBS with sham TBS as an add-on to antidepressant medication showed no significant benefits over a short treatment period of 10 sessions in two weeks only [13]. To our knowledge, there is a critical lack of RCTs investigating the efficacy of iTBS for depressive symptoms in adolescents and young adults without concomitant pharmacotherapy. Moreover, studies have not assessed long-term treatment effects over several months. Given the broad spectrum of potential iTBS settings and the ongoing neurodevelopmental processes in younger individuals–which may alter their treatment response compared to adults [14]–it is likely that parameters such as stimulation dose, treatment target, frequency, duration, and patient selection criteria, need to be systematically refined to achieve optimal results in later confirmatory trials. In traditional research frameworks, such optimizations are typically conducted through multiple pilot trials. This approach often leads to protracted, resource-intensive development processes and a high risk of early false positive findings [15]. For example, recent multicenter RCTs investigating transcranial direct current stimulation (tDCS) for MDD within a narrow set of treatment parameters despite a lack of robust early clinical validation [16–18], have resulted in inconsistent findings and provided limited guidance on how to improve the efficacy of the intervention [19]. In contrast, adaptive trial designs, initially developed in oncology, offer an alternative research strategy. These designs allow for more efficient and systematic testing of promising novel interventions. The use of adaptive designs within mental health has been increasingly advocated to leverage innovation and accelerate treatment development [15, 20].

In the EARLY-BURST pilot trial, we aim to assess the efficacy and safety of a six-week course of iTBS targeting the left DLPFC versus sham iTBS in reducing depressive symptoms in treatment-seeking adolescents and young adults with MDD, persistent depressive disorder (PDD), or bipolar disorder with current depression (BD) who have not received antidepressant or antipsychotic medication in the past year, except for short-term on-demand use (less than 2 weeks). On an exploratory basis, we will compare treatment groups across the domains of self-reported depression, anxiety, stress, anhedonia, functioning, and over a 6 month follow-up period. To optimize the use of research resources, our study will employ a Bayesian sequential analysis design [15, 21], which facilitates the early detection of effective vs ineffective treatment protocols [22]. This approach not only promises to reduce the burden on participants in the event of negative outcomes but, crucially, also enables the trial to be transformed into an adaptive multi-arm design, where protocol refinements can be iteratively tested to further enhance the efficacy of the intervention. We currently seek additional funding for such an extension.

## Methods

### Trial design

The EARLY-BURST trial is a sequential Bayesian, randomized, double-blind, parallel-group, sham-controlled pilot trial testing the superiority of six weeks of intermittent theta burst stimulation (iTBS) of the left dorsolateral prefrontal cortex (lDLPFC) versus sham iTBS (see Fig. 1). The primary outcome will be the difference in depression severity at week 6 (post-treatment visit) between active iTBS and sham iTBS, assessed with the Montgomery-Åsberg Depression Rating Scale (MADRS).

**Fig. 1 Fig1:**
[figure not shown]
Treatment groups

Trial outcomes and exploratory measures will be assessed in person at the participating study centers using the CentraXX patient app (https://www.kairos.de/en/products/centraxx-patient-app/). Study visits are scheduled for screening, at baseline, at two-time points during treatment (week 2 and week 4), and upon completion of the intervention (week 6; see Fig. 2). Follow-up visits will be conducted three and six months after randomization. All patients are required to provide written informed consent prior to participating in any study-related procedures. The trial started recruitment of patients in April 2024 and will continue recruiting until April 2027. The study will be reported in accordance with the Consolidated Standards of Reporting Trials Statement 2010 and the extensions for reporting randomized pilot and feasibility trials [23], for reporting outcomes in clinical trials [24], and the template for intervention description and replication (TIDieR) checklist [25]. This trial protocol follows the SPIRIT guideline [26].

**Fig. 2 Fig2:**
[figure not shown]
Study flow. *N*_max_ maximum sample size, *iTBS* intermittent theta burst stimulation, *ITT* intention-to-treat, *W* weeks, *V* visit, *M* months, *FU* follow-up

### Study setting

The trial will be conducted in an urban setting in Germany at the Center for Non-invasive Brain Stimulation Munich-Augsburg (CNBS^MA^), a specialized in- and outpatient service at the LMU University Hospital Munich's Departments of Psychiatry and Psychotherapy and Child and Adolescent Psychiatry, Psychosomatics and Psychotherapy and the University of Augsburg's Department of Psychiatry, Psychotherapy, and Psychosomatics.

### Participants

Overall, a maximum of 90 treatment-seeking female, male, and non-binary in-and out-patients with depressive disorders and no antidepressant or antipsychotic medication during the last 12 months, except for short-term (< 2 weeks) on-demand medication, are planned to be recruited. We will allow co-morbidities, except for severe psychopathology, likely to interfere with the study procedures and conditions unlikely to benefit from treatment. Inclusion criteria are (1) age 16–26 years; (2) diagnosis of MDD, PDD, or BD (Diagnostic and Statistical Manual of Mental Disorders, Fifth Edition, [DSM-5] criteria; assessed with the Diagnostic Interview for Mental Disorders [DIPS]); (3) no antidepressant or antipsychotic medication during the last 12 months, except for short-term (< 2 weeks) on-demand medication; (4) fluent in reading and speaking German; (5) capable and willing to provide informed consent (has to be confirmed by an independent physician; in the case of minors, the consent of the legal guardians will be obtained). Exclusion criteria are (1) positive screening for acute mania (defined by reaching the threshold “mild or greater” on at least one question from the Adult DSM-5 Self-Rated Level 1 Cross-Cutting Symptom Measure [from here on referred to as “APA screener”] Mania domain); (2) positive screening for acute psychosis (defined by reaching the threshold “slight or greater” on at least one question from the APA screener Psychosis domain); (3) positive screening for Obsessive–Compulsive Disorder (defined by reaching the threshold “mild or greater” on at least one question from the APA screener Repetitive Thoughts and Behaviors domain); (4) severe borderline typical psychopathology, defined as a very-high mean score on the self-reported Borderline Symptom List (BSL-23) of ≥ 2.67; (5) primary substance use disorder except for nicotine and caffeine (DSM-5, assessed with the DIPS); (6) acute risk for suicidality, assessed by the Columbia Suicide Severity Rating Scale (C-SSRS; patient agrees to item 4 and/or item 5); (7) history of brain surgery, significant and clinically relevant brain malformation or neoplasm, head injury, stroke, dementia or other neurodegenerative disorder; (8) history of seizures; (9) previous brain stimulation treatment (rTMS, transcranial direct current stimulation, electroconvulsive therapy, vagus nerve stimulation, deep brain stimulation); (10) cardiac pacemakers, intracranial implants, or metal in the cranium; (11) antiepileptic drugs and/or benzodiazepines corresponding to > 1 mg lorazepam/day; (12) severe somatic comorbidity as judged by the study physician; (13) pregnancy (negative urine HCG test in women); (14) any clinically relevant findings in a structural MRI safety check (evaluated by a neuroradiologist); (15) investigators, site personnel directly affiliated with this study, and their immediate families (immediate family is defined as a spouse, parent, child or sibling, whether by birth or legal adoption). Participants will be recruited after referral or personal inquiry at the CNBS^MA^ using offline and online materials approved by the institutional ethics committee.

### Randomization, assignment concealment, and blinding

Eligible patients will be randomized 1:1 to the active iTBS or sham iTBS treatment arms. An independent statistician ([name]) will do the randomization, using an in-house R script (with random sequences from random.org) to generate randomly permuted blocks of varying lengths, stratified by study sites (LMU University Hospital vs. University of Augsburg) and biological sex at birth. After baseline assessments, clinical raters will provide participant stratification information to [name]. [name] will then send one of two non-descriptive, alphanumeric codes via mail to the TMS operators, matching markings on either the active iTBS or sham iTBS coil. The markings will be applied by an independent clinician not involved in the administration, recruitment, treatment, medical oversight, analysis, or any other study-related procedure prior to the study initiation. Apart from the non-descriptive markings, the sham coils look identical to the active stimulation coils, generate identical sounds, and have similar weights. Furthermore, they emit minimal magnetic field strengths with which only the nearest area (such as the scalp) is stimulated, producing a twitching sensation without neural activity. Thus, operators will be able to select the correct coil while remaining blinded to the treatment condition. Study raters will not be involved in the treatment sessions and thus will be kept blinded. Treatment conditions will be revealed after the final study analysis has been conducted.

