### Primary outcome

The primary outcome will be the difference in MADRS scores at week 6 (post-treatment visit) between active iTBS and sham iTBS, controlling for baseline MADRS scores. The MADRS is a clinician-rated measure of depression severity that assesses ten common depressive symptoms (apparent sadness, reported sadness, inner tension, reduced sleep, reduced appetite, concentration difficulties, lassitude, inability to feel, pessimistic thoughts, and suicidal thoughts) on a scale from 0–6. The overall score ranges from 0 to 60, with higher MADRS scores indicating more severe depression. We will use the structured interview guide for the MADRS (SIGMA)[30] to improve the reliability of assessments between study raters. All raters will receive video-based SIGMA training, during which they will rate two example video interviews.

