### Statistical methods and analysis

This protocol pre-specifies only the primary sequential analyses; others are exploratory. Safety assessments will be descriptive. All analyses will be conducted in R [42]. The analysis scripts are available at 10.17605/OSF.IO/B397U.

Following the methodology of Blackwell et al. [15], we will employ sequential analyses (see Fig. 3) with directional Bayes factors (BFs) to assess the efficacy of active and sham iTBS on the primary outcome. BFs [43] essentially calculate the probability of the observed data under the alternative hypothesis (active iTBS reduces MADRS scores more than sham) divided by the probability of the observed data under the null hypothesis (no superiority of active iTBS). The progression of the trial depends on pre-defined parameters: the minimal sample size per arm, N_min_, at which sequential analyses are initiated; a maximum sample size, N_max_; a BF threshold indicating lack of superiority, BF_fail_; and a BF threshold indicating superiority, BF_success_. The specific parameter set was determined by simulation (see below). The trial will halt upon reaching any threshold or N_max_. In the latter case, discussions on extending recruitment may occur with the funder, pending additional ethical approval. Participants ongoing in treatment at trial cessation will complete it, with their data included in final analyses but not in further sequential analyses.

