**Fig. 3 Fig3:**
[figure not shown]
Sequential Bayesian analysis design

Analyses will follow an intention-to-treat approach, including all participants randomized to a condition, irrespective of intervention completion or outcome data availability. For sensitivity analyses, participants will be classified as per protocol if they complete the 6-week treatment period and receive at least 20 treatment sessions within six weeks. Sequential analyses will commence once each arm meets the predefined minimum sample size N_min_. Analyses will be updated with each participant’s trial completion. Following Blackwell et al. (2022), missing data will be handled using constrained longitudinal data analysis (cLDA) via the R package nlme [44]. Bayes factors will be estimated with the R package BayesFactor [45] using the t-statistic for the Time x Group interaction and directional default Cauchy prior (rscale parameter = √2/2). Effect sizes (adjusted Cohen's d) and estimated means for the primary outcome, along with their 95% confidence intervals (CIs), will be derived from the cLDA model using the R packages effectsize [46] and emmeans [47]. Analyses will be performed by a statistician ([name]) aware of participant allocation (given the directional nature of the analyses), sharing results with the research team only if a BF boundary is met or after N_max_ is reached.

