### Sample size calculation

Using pairwise comparison simulations, we set analysis parameters to achieve a false-positive rate of < 5% and a power of ~ 80% for detecting an effect size of d = 0.6. The choice of effect size was revised after the trial commenced but prior to the start of sequential analysis, based on a recent meta-analysis of iTBS [48]. Initially, we selected an effect-size of 0.8 due to practical considerations, including the absence of specific evidence for iTBS in younger populations and constraints on trial funding. For N_min_ = 26; N_max_ = 45; BF_fail_ = 1/5; and BF_success_ = 5, simulations with up to 15% missing data suggest that these parameters provide a < 5% false-positive rate and 71.35% power to reach the BF_fail_ threshold before recruitment of N_max_ when d = 0; and 81% power to hit BF_success_ before N_max_ for an effect size of d = 0.6(see Table 2). For practical purposes, N_max_ will be operationalized on the basis of the total sample size, that is, when the total number of participants randomized is 2 × N_max_ (i.e., *N* = 90), regardless of the distribution across arms. Simulation scripts and results of the initial and revised sample size calculations are available at 10.17605/OSF.IO/B397U.

**Table 2 Tab2:** Pairwise comparison simulations using cLDA

	Probability of hitting BF threshold at each participant number (per group)									
	Hit BFfail					Hit BFsuccess				
d	26	30	35	40	45	26	30	35	40	45
− 0.2	73.85	82.45	87.20	90.90	93.40	0.20	0.45	0.45	0.70	0.70
0	46.20	55.60	62.05	67.20	71.35	**1.30**	**1.95**	**2.45**	**2.75**	**3.00**
0.2	18.85	25.15	30.15	33.40	35.40	6.20	9.95	13.10	15.75	17.95
0.3	11.45	15.90	18.65	20.40	22.10	12.85	18.05	22.25	26.50	29.55
0.4	5.45	7.25	8.55	9.70	10.15	21.85	31.10	37.55	42.75	47.45
0.51	2.00	2.95	3.40	3.85	4.00	34.65	45.60	54.10	60.25	66.55
0.6	1.25	1.55	1.85	1.95	2.00	**48.95**	**60.25**	**69.45**	**76.25**	**81.15**
0.71	0.30	0.50	0.55	0.55	0.55	63.10	74.65	82.55	87.15	91.10
0.8	0.05	0.20	0.20	0.20	0.20	74.15	83.35	89.80	92.65	95.35

Bold values indicate false-positive rate and power estimates for an effect size of 0.6

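### Randomization is stratified by site and sex, but the primary model as described names neither; adding both before the first look is a cheap gain in precision if they are prognostic

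*Protocol article*

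**What the plan says.** - **Allocation** (Randomization, assignment concealment, and blinding): "Eligible patients will be randomized 1:1 to the active iTBS or sham iTBS treatment arms", in permuted blocks of varying length, "stratified by study sites (LMU University Hospital vs. University of Augsburg) and biological sex at birth".
- **Primary comparison** (Primary outcome): week-6 MADRS between arms, "controlling for baseline MADRS scores". No other covariate is named.
- **Model** (Statistical methods and analysis, text after Fig. 3): "missing data will be handled using constrained longitudinal data analysis (cLDA) via the R package nlme". The Bayes factor is computed "using the t-statistic for the Time x Group interaction and directional default Cauchy prior (rscale parameter = √2/2").
- **Status of this analysis** (Statistical methods and analysis): "This protocol pre-specifies only the primary sequential analyses; others are exploratory". The code is referred to, not printed: "The analysis scripts are available at 10.17605/OSF.IO/B397U".
- **Design parameters** (Sample size calculation): "For N_min_ = 26; N_max_ = 45; BF_fail_ = 1/5; and BF_success_ = 5". Table 2 gives 81.15% power at d = 0.6, and 3.00% false positives and 71.35% reaching BF_fail at d = 0, with 15% missing data.

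Site and sex appear nowhere in the described analysis or in the description of the simulations. The article prints no full model formula, does not say that the factors are left out, and gives no figure for how strongly either predicts week-6 MADRS.

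**The concern.** Stratified blocks balance the arms on site and sex, so differences between strata drop out of the true sampling error of the treatment effect. A model without the strata still counts those differences as residual noise. Its standard error is then larger than the true sampling error, and the t-statistic that feeds the Bayes factor is too close to zero. What is at stake is efficiency: a lower chance of reaching BF_success in a trial capped at 90 participants, whose stated power of 81.15% is about one point above its target of roughly 80%.

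A site effect on week 6 need not be visible at baseline. Sessions are given in person at each site, concurrent psychotherapy and psychosocial care are allowed (Intervention), and only the Munich centre lists a child and adolescent department (Study setting).

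Timing matters too. The sequential analyses are updated with each completer by a statistician who knows the allocation. Covariates added after the looks begin would be hard to defend.

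**Working it through.** **Inputs from the article.** 1:1 allocation; looks from 26 to 45 per arm; BF boundaries 1/5 and 5; one-sided Cauchy prior with r = √2/2; 15% missing; d on the change-score scale.

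**Assumptions, not in the article.** Pre-post correlation ρ = 0.5; site split 70/30; sex split 65/35; blocks of 2 or 4; baseline-adjusted regression on completers as a stand-in for cLDA. R² is the share of week-6 variance, given baseline, that site and sex explain.

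**Step 1: reproduce the stated figures.** The boundaries were turned into t cut-offs from

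BF(t) = ∫₀^∞ f(t; ν, δ√(n/2)) · 2/[πr(1 + δ²/r²)] dδ ÷ f(t; ν, 0),

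where f is the (noncentral) t density, and the sequential design was then simulated.

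| Quantity at 45 per arm | Stated | n = per-arm patients (4,000 runs) | n ≈ 1.85 × per-arm, i.e. observations (10,000 runs) |
|---|---|---|---|
| Power, d = 0.6 | 81.15% | 80.6% | 79.9% |
| False positive, d = 0 | 3.00% | 2.7% | 2.9% |
| BF_fail, d = 0 | 71.35% | 57.4% | 72.5% |

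Power and false-positive rate are close under both codings. BF_fail is matched only with the larger n, so the larger n is used in Steps 2 and 3.

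**Step 2: standard error.** With SD 1 at each visit, the baseline-adjusted residual SD is √(1 − 0.5²) = 0.866. With 45 × 0.85 = 38.25 completers per arm, SE = 0.866 × √(2/38.25) = 0.198 (simulated 0.199). Adding strata that explain R² should multiply the model SE by about √(1 − R²): 0.990, 0.975 and 0.949 at 2, 5 and 10%. The simulated ratios are 0.992, 0.977 and 0.950. At R² = 10% the unadjusted model SE is 0.199 against an empirical SE of 0.192, so it is about 3.5% too large. At R² = 0 it is not too large (0.199 against 0.201).

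**Step 3: operating characteristics.** 6,000 runs per cell, both models fitted to the same simulated data.

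| Prognostic strength (assumed) | SE ratio | Power at d = 0.6, unadjusted → adjusted | Change | False positive, unadjusted → adjusted |
|---|---|---|---|---|
| R² = 0% | 1.003 | 79.5 → 79.0% | -0.4 | 3.1 → 3.0% |
| R² = 2% | 0.992 | 79.4 → 80.0% | +0.6 | 3.0 → 3.0% |
| R² = 5% | 0.977 | 79.7 → 81.4% | +1.7 | 2.8 → 3.0% |
| R² = 10% | 0.950 | 80.2 → 83.6% | +3.3 | 2.5 → 3.0% |
| Constant shift, 5% of total variance | 0.994 | 79.5 → 79.8% | +0.3 | 3.0 → 3.0% |
| Constant shift, 10% of total variance | 0.984 | 79.6 → 80.7% | +1.1 | 3.0 → 3.0% |

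A constant shift is the same at baseline and week 6, so the baseline score absorbs most of it. At R² = 20%, which would be strong for these two factors, power goes from 80.9 to 87.7%.

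A second simulation, with arms balanced within stratum and 8,000 runs per cell, gave 81.5 → 82.9% at R² = 5% (+1.4) and 81.8 → 84.9% at 10% (+3.1). Its false-positive rate after adjustment was 3.5%.

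**Step 4: which boundary is affected.** Solving BF = 5 gives a BF_success cut-off in t of roughly 2.35 to 2.42, so shrinkage towards zero always makes it harder to reach. Solving BF = 1/5 gives a BF_fail cut-off of -0.51 at 26 per arm, rising to -0.14 at 45, if n is the per-arm number. With the larger n it is -0.10 at 26, +0.08 at 35, +0.16 at 40 and +0.22 at 45. Shrinkage makes a negative cut-off harder to reach and a positive one easier. The direction for BF_fail therefore depends on coding that is not shown.

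**The case against.** The strongest reply is that this argues from silence. The article is condensed, prints no formula and points to posted scripts. Controlling for baseline describes the contrast and is not a closed list of covariates. That stands: the documents do not show that the fitted model leaves site and sex out, and the sections do not contradict each other. However, the article describes its one pre-specified analysis down to the prior scale and names a single covariate. Recommending a better model than the one described is therefore more than asking for missing detail.

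A reader might infer more than the documents support:

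- **That the standard error is too large.** This holds only if site or sex predicts week 6 beyond baseline. At R² = 0, adjustment loses a little.
- **That both boundaries are crossed late.** This holds for BF_success. For BF_fail it can go either way (Step 4).
- **That the benefit of stratifying is lost.** Balance between arms is kept; only some precision is forgone.
- **That the stated error rate or power is wrong.** The unadjusted error is conservative, and the stated figures reproduce to within two points at 45 per arm without the strata.

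**Conclusion.** The point holds as a conditional efficiency improvement with medium confidence. It is not an error and does not threaten validity. The model as described does not use the randomization strata. If they are prognostic beyond baseline, adjustment is worth well under one power point at R² = 2%, about one and a half at 5% and about three at 10%. If they are not, it costs about half a point. The false-positive rate stays below the stated limit in every case examined. These sizes rest on the assumed R², the assumed correlation of 0.5 and the regression approximation to cLDA. A different correlation would move the power levels themselves: unadjusted power was about 86% at 0.3 and 76% at 0.7.

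**What to change.** Before the first sequential look, specify in the primary cLDA site and sex at birth, each with its interaction with time so that they adjust the week-6 contrast, and use that model at every look. If the posted scripts already contain these terms, say so in the text. Rerun Table 2 with the chosen model, and state which n enters the Bayes factor. The amendment with revised sample size calculations that is already being prepared (Ethical approval and dissemination) is the natural place, since only one participant had been enrolled at submission (Trial status).

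Cost: four fixed-effect parameters in a two-occasion model, of which two bear on the week-6 contrast, and more if the week 2 and week 4 visits enter the model. In addition there is one simulation rerun, and about half a power point if neither factor is prognostic. Both variables are known at randomization, so no new data are needed.
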